### Sample size

In this study, time to radiologic healing is the primary objective. This is a well-accepted quantitative approach to evaluate fracture union, as in our previous study [21]. We expect 20% acceleration of radiologic healing time (our animal data confirms 30% acceleration [9]). A sample size of 100 will detect a significant difference using ANOVA with 80% power and 0.05 significance level (PASS 11.0, NCSS, LLC, Utah, USA). Our previous clinical trial [17] confirmed that compliance of vibration treatment was very good with normal subjects at 66% on average [17]. We conservatively increase the sample size to 120, assuming 15% dropout rate.

### Randomization and blinding

Patients will be actively screened and recruited from the Department of Orthopaedics and Traumatology, Prince of Wales Hospital, Hospital Authority, Hong Kong, based on inclusion and exclusion criteria. According to our previously established protocol [22], a computer-generated set of random allocations are sealed in consecutively numbered opaque envelopes by an independent central technician. Once consent is obtained, the patient is randomized and assigned into either vibration or placebo group by opening the next sealed envelope by a specific staff member. Patients and investigators are fully blinded until the completion of treatment. Outcome assessors and statistician are blinded.

Patient demographics will be recorded and confirmed with the Clinical Management System (CMS), Hospital Authority, which is the central electronic database for public hospitals in Hong Kong [23]. Before signing the consent form, each patient will be explained the objectives, benefits, and risks of the study and their rights and responsibilities, as well as privacy and confidentiality information. An information sheet will also be distributed.

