**Methods:**

This is a randomized, double-blinded, placebo-controlled clinical trial to evaluate the effect of LMHFV in accelerating trochanteric hip fracture healing. All fractures undergo cephalomedullary nail fixation. The primary outcome of this study is time to fracture healing by X-ray. Computed tomography (CT) and dual-energy X-ray absorptiometry (DXA) will also be performed. Blood circulation at the fracture site will be assessed by dynamic perfusion magnetic resonance (MR). Clinical results include functional recovery by muscle strength, timed up and go test (TUG), quality of life questionnaire (SF-36), balancing, falls, and mortality.

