### Interventions

Patients will be randomly allocated to placebo or vibration group [22]. Vibration is treated with LMHFV (V-health Ltd, Hong Kong) at 35 Hz, 0.3 g (*g* = gravitational acceleration) for 20 min/day, 5 times/week [17], while the placebo group will have sham treatment to stand on the LMHFV platform for 20 min/day, 5 times/week. Sound emitted by machine masks the noise an active machine makes [24]. Treatment is started at 3 days post-operation for a total of 14 days (protocol change from 6 months due to COVID-19 for patient feasibility). Patients will be followed up to 6 months.

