## Outcome assessments

### Plain radiographs

Anteroposterior and lateral X-ray (DRX-Evolution, Carestream Health, Rochester, NY, USA) of fracture site will be performed at baseline, 6, 12, and 26 weeks post-operation. Films will be assessed by two blinded surgeons independently, to note healing in the AP or lateral film [21]. Fracture healing is defined based on the Radiographic Union Score of Hip (RUSH), which assesses callus formation and visibility of fracture line at 4 cortices [25].

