### Functional and quality of life outcomes

At baseline, 2, 6, 12, and 26 weeks post-operation, all patients will be assessed with the following functional tests:

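### Blinding of patients and investigators is guaranteed only to the end of treatment, now about day 17, while follow-up and most self-reported and effort-dependent outcomes run to week 26

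*Protocol article*

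**What the plan says.** Randomization and blinding makes two separate statements. For patients and investigators it gives an end point: "Patients and investigators are fully blinded until the completion of treatment". For those who measure and analyse, it gives none: "Outcome assessors and statistician are blinded". The Plain radiographs section adds that two blinded surgeons read the films independently, again with no time limit.

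Interventions sets the length of treatment: "Treatment is started at 3 days post-operation for a total of 14 days (protocol change from 6 months due to COVID-19 for patient feasibility". Both arms attend five times a week; the control arm receives "sham treatment to stand on the LMHFV platform for 20 min/day, 5 times/week". The same section says: "Patients will be followed up to 6 months".

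The abstract states: "The primary outcome of this study is time to fracture healing by X-ray". X-rays "of fracture site will be performed at baseline, 6, 12, and 26 weeks post-operation". Pain, SF-36, quadriceps strength, balance and the timed up and go test are scheduled thus: "At baseline, 2, 6, 12, and 26 weeks post-operation". The Falls section uses a fall calendar, with time points of 1 month, 3 months and 1 year.

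Table 1 in the Appendix places the trial's treatments in months 1-12 and its outcome assessments in months 1-18.

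**The concern.** The trial is described as double-blinded and placebo-controlled, but its rule ties the blinding of two of the four named groups to the end of a short treatment period. Once a patient's last session is over, telling that patient or an investigator the allocation would not breach the protocol as worded.

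What is at stake differs by outcome.

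- **Self-reported outcomes** (verbal descriptor pain scale, SF-36, fall calendar): the patient is the source of the data. A blinded assessor who records the answer of a patient who knows the allocation does not obtain a blinded measurement.
- **Effort-dependent tests** (timed up and go, maximal quadriceps force, balance): the patient sets the effort, so expectation can affect the result even with a blinded tester.
- **Time to radiographic healing:** film reading is blinded. What remains is indirect: knowledge of allocation could alter co-interventions such as physiotherapy and analgesia, attendance at the three post-baseline films, or dropout.

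Bias of this kind cannot be removed at analysis, because blinding that has been lost cannot be restored.

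**Working it through.** The article gives no figure for the length of blinding, so there is none to reproduce. The check compares the day treatment ends with the day of each assessment.

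**Inputs.** Treatment starts on day 3, lasts 14 days, and has 5 sessions a week (Interventions). X-rays are at weeks 6, 12 and 26 (Plain radiographs). Functional visits are at weeks 2, 6, 12 and 26 (Functional and quality of life outcomes). Treatment runs in months 1-12 and assessments in months 1-18 (Table 1).

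**Step 1: end of treatment for one patient.**

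- 14 calendar days counted inclusively: 3 + 13 = day 16.
- Start plus 14 days: 3 + 14 = day 17.
- 14 sessions at five a week, assuming sessions on weekdays only: day 20 to day 22, depending on the weekday of the start.

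**Step 2: assessment days (weeks × 7).** Week 2 = day 14, week 6 = day 42, week 12 = day 84, week 26 = day 182.

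**Step 3: visits after the guaranteed period.**

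| Post-baseline visits | Days | After day 16 | After day 17 | After day 22 |
|---|---|---|---|---|
| X-ray | 42, 84, 182 | 3 of 3 | 3 of 3 | 3 of 3 |
| Functional, pain, SF-36 | 14, 42, 84, 182 | 3 of 4 | 3 of 4 | 3 of 4 |

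The counts do not depend on how the 14 days are read. Only the week 2 visit is covered. The first X-ray comes 42 − 17 = 25 days after day 17. All fall-calendar time points also come later, since the earliest is 1 month.

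**Step 4: share of follow-up after the guaranteed period.**

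- From day 16: (182 − 16)/182 = 166/182 = 91%.
- From day 17: (182 − 17)/182 = 165/182 = 91%.
- From day 22: (182 − 22)/182 = 160/182 = 88%.

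**Step 5: the other reading.** Suppose the phrase means the end of treatment for the whole trial, at month 12. Assume uniform enrolment over 12 months and 6 months of follow-up each. A patient enrolled at month t > 6 then has t − 6 months of follow-up after month 12. The average over all patients is (1/12) × (6²/2) = 18/12 = 1.5 months, and 1.5/6 = 25% of follow-up time. The gap is smaller, but those enrolled in the second half of the year are still exposed.

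**Step 6: effect of the fix.** If blinding ran through the last 26-week assessment, it would cover 3 of 3 post-baseline X-ray visits and 4 of 4 functional visits, against 0 of 3 and 1 of 4 as written on the per-patient reading. No sample size figure changes.

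**The case against.** The strongest reply is that the primary outcome is already protected where it matters most. A reader might infer that the X-ray readings themselves are open to bias because all three post-baseline films fall after treatment. The documents do not support this: assessors and statistician are declared blinded with no end date, and the film readers are separately described as blinded. CT is also read by a blinded radiologist, mortality comes from a central record system, and bone density and perfusion are instrument measurements. This part of the objection stands in full.

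Second, a reader might infer that unblinding is planned. It is not. The sentence sets a minimum, and the article describes no step at which allocation is revealed. Blinding may in practice continue to week 26. This also stands: the defect is a rule that permits unblinding, and no actual loss of blinding is shown.

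Third, it is tempting to say that the sentence was written for six months of treatment and overlooked when treatment was shortened. That is plausible, but the former protocol text is not shown. Trial status says that the assessment time points changed too, so the original follow-up length is unknown.

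Fourth, the end of treatment may refer to the trial's treatment phase. On the enrolment assumption above, that reduces the uncovered share to about 25%, so 88-91% is not the only possible figure. It does not close the gap.

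Finally, an article condenses the full protocol, and emergency-unblinding procedures or staff roles may properly be left to that document. The point here does not rest on such omissions, but on an end point that the article states explicitly.

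**Conclusion.** The point holds at the level of should-fix. As written, the guarantee for patients and investigators stops well before follow-up does. On the per-patient reading it ends between day 16 and day 22, and the visit counts in the working are the same under every way of counting the 14 days. The 88-91% share rests on that reading; the 25% share rests on the trial-phase reading with uniform enrolment.

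The direct exposure is confined to secondary outcomes that patients report or perform. For the primary outcome the exposure is indirect, and the documents give no basis for putting a size on it. Because film reading is protected and unblinding is only permitted, the point does not call the primary analysis into question. It does mean that the double-blind description is not secured by the stated rule for most of follow-up.

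**What to change.** Replace the sentence on patients and investigators in Randomization and blinding with wording such as: *Patients and investigators remain blinded until the last patient's 26-week assessment is complete; outcome assessors and the statistician also remain blinded.* This removes both the ambiguity about whose treatment is meant and the dependence on treatment length. If the 1-year time point in the Falls section is kept, the end point should be set at that last fall-calendar assessment instead, since falls are self-reported.

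The cost is one sentence and an instruction to staff. Patients learn their allocation later than the present wording would allow. No patients, visits or procedures are added, and the treatment schedule is unaffected.

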### Interventions

Patients will be randomly allocated to placebo or vibration group [22]. Vibration is treated with LMHFV (V-health Ltd, Hong Kong) at 35 Hz, 0.3 g (*g* = gravitational acceleration) for 20 min/day, 5 times/week [17], while the placebo group will have sham treatment to stand on the LMHFV platform for 20 min/day, 5 times/week. Sound emitted by machine masks the noise an active machine makes [24]. Treatment is started at 3 days post-operation for a total of 14 days (protocol change from 6 months due to COVID-19 for patient feasibility). Patients will be followed up to 6 months.

## Outcome assessments

### Plain radiographs

Anteroposterior and lateral X-ray (DRX-Evolution, Carestream Health, Rochester, NY, USA) of fracture site will be performed at baseline, 6, 12, and 26 weeks post-operation. Films will be assessed by two blinded surgeons independently, to note healing in the AP or lateral film [21]. Fracture healing is defined based on the Radiographic Union Score of Hip (RUSH), which assesses callus formation and visibility of fracture line at 4 cortices [25].

### Computed tomography (CT)

CT (SOMATOM Drive, Siemens, Erlangen, Germany) scan will be performed at the region of interest 5 cm proximal and distal to the fracture site [26], at baseline, 6, and 12 weeks post-operation. Films will be assessed by a blinded radiologist.

### Clinical monitoring

Standard postoperative program for all in-patients, including vital sign monitoring, wound condition, neurovascular status, pain, analgesic, and mobilization.

### Densitometry status

Bone mineral density (BMD) and bone mineral content (BMC) will be measured at baseline, 6, 12, and 26 weeks post-operation using DXA (Horizon DXA System, Hologic Inc., USA) to monitor changes in bone quality at the fracture site [18].

### Dynamic perfusion MRI

Blood circulation at fracture site will be measured at baseline and 6 weeks post-operation with dynamic contrast-enhanced MR imaging (Intera NT; Philips Medical Systems, Best, Netherlands) with maximum gradient strength of 30 mT/m as in our previously established protocol [27, 28].

### Functional and quality of life outcomes

At baseline, 2, 6, 12, and 26 weeks post-operation, all patients will be assessed with the following functional tests:

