## Abstract

**Background:**

There are more than 300,000 hip fractures yearly in the USA with mortality rates of 20% within 1 year. The treatment of osteoporotic fractures is a major challenge as bone quality is poor, and healing is expected to delay due to the impaired healing properties with respect to bone formation, angiogenesis, and mineralization. Enhancement of osteoporotic fracture healing and function is therefore critical as a major goal in modern fracture management. Previous pre-clinical studies have shown that low-magnitude high-frequency vibration (LMHFV) accelerates osteoporotic fracture healing. The objective of this study is to investigate the effect of LMHFV on accelerating trochanteric hip fracture healing and functional recovery.

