## Methods

### Study design and standardization of surgical management

This is a randomized, double-blinded, placebo-controlled clinical trial to evaluate the effect of LMHFV (VH-001 exercise platform; V-health Limited, Hong Kong) on accelerating trochanteric hip fracture healing (Fig. 1). Trochanteric hip fracture patients admitted to the Orthopaedics and Traumatology ward are recruited, which are from the Prince of Wales Hospital, affiliated with the Chinese University of Hong Kong. All patients would be screened for the inclusion and exclusion criteria to meet eligibility for the study. There are more than 400 hip fractures admitted to our unit each year. Closed reduction and cephalomedullary nail fixation (Gamma3 nail, Stryker, USA) [19] will be performed for all patients within 48 h. Orthogeriatric co-care is provided for each patient to assess and treat any medical complications before operation [20]. Prophylactic intravenous antibiotic with cefazolin 1 g is given before surgical incision and continued for 3 doses after every 8 h. Postoperatively, pressure bandage will be given until mobilization. Adequate analgesics will be given. Full weight bearing with physiotherapy is started as soon as condition allows.

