### Statistics

All results will be expressed in mean ± standard deviation. Statistical analysis will be performed using SPSS (IBM, NY, USA). One-way (for between-group differences in over-time changes), two-way (for interaction effect among time and group), and group repeated measures ANOVA with post-hoc Bonferroni analysis, as well as independent/paired *t* tests will be performed. Significance level is set at *p* < 0.05 (2-tailed).

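### Secondary functional comparisons use only a post-fracture baseline and name no covariate, which can cost precision; adjusting for pre-fracture mobility is a cheap improvement

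*Protocol article*

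**What the plan says.** The abstract puts function in the objective: "The objective of this study is to investigate the effect of LMHFV on accelerating trochanteric hip fracture healing and functional recovery". It then lists the measures: "Clinical results include functional recovery by muscle strength, timed up and go test (TUG), quality of life questionnaire (SF-36), balancing, falls, and mortality". The Background section places function and quality of life among the secondary outcomes.

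The schedule under Functional and quality of life outcomes is: "At baseline, 2, 6, 12, and 26 weeks post-operation, all patients will be assessed with the following functional tests". Under Study design and standardization of surgical management, "Trochanteric hip fracture patients admitted to the Orthopaedics and Traumatology ward are recruited". Under Interventions, "Treatment is started at 3 days post-operation for a total of 14 days". A baseline measured in this trial is therefore a post-fracture value.

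The Statistics section gives the analyses as "One-way (for between-group differences in over-time changes), two-way (for interaction effect among time and group"), then "group repeated measures ANOVA with post-hoc Bonferroni analysis, as well as independent/paired" t tests. It names no covariate. The Randomization and blinding section says that demographics are recorded and confirmed against the hospital's Clinical Management System (CMS), without itemising them. The eligibility lists exclude chairbound or bedbound patients but set no other mobility limit. The article names no measure of mobility before the fracture.

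**The concern.** Patients aged 65 or over who were not chairbound or bedbound can differ widely in how well they walked before the fall, and that is likely to predict strength, balance, TUG and SF-36 months later. The only functional reference in the article is a value taken in the days around surgery, which may predict later function poorly.

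Two costs follow if so. Subtracting a weakly correlated baseline adds noise rather than removing it. A prognostic variable that could be had for one question at enrolment stays in the error term. Real differences in the secondary functional outcomes would then be harder to detect, and the functional results harder to put in context. The item is best collected at entry: later recall is weaker and would follow allocation.

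**Working it through.** **The plan's own figure.** The Sample size section gives 100 patients, raised to 120 for 15% dropout: 100/(1 − 0.15) = 117.6, or 118, which agrees with 120 after rounding up. This concerns radiologic healing time. No figure is given for any functional outcome, so what follows is a range under assumptions.

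**Inputs.**
- From the article: 120 patients, 15% dropout, two-sided 5% level.
- Assumed: 1:1 allocation, so 120 × 0.85 / 2 = 51 per arm; a true standardised difference d of 0.5 or 0.4; correlation r of the acute baseline with follow-up of 0.1–0.3; correlation q of pre-fracture mobility with follow-up of 0.4–0.6; equal SDs at baseline and follow-up unless stated.

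**Variance of the arm difference, relative to the follow-up value alone (= 1).**
- Change score: 2(1 − r). At r = 0.1 this is 1.8; at r = 0.3 it is 1.4. It falls below 1 only when r exceeds 0.5.
- Adjusted for the acute baseline: 1 − r² = 0.99 to 0.91.
- Adjusted for pre-fracture mobility: 1 − q² = 0.84 to 0.64.

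**Power** (two-sample t test, noncentral t, effect = d/√(relative variance)):

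| Analysis | d = 0.5 | d = 0.4 |
|---|---|---|
| Change score, r = 0.1–0.3 | 46–56% | 32–39% |
| Follow-up value alone | 71% | 52% |
| Adjusted for acute baseline, r = 0.1–0.3 | 71–75% | 52–55% |
| Adjusted for pre-fracture mobility, q = 0.4–0.6 | 78–88% | 59–71% |

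For example, the change score at r = 0.1 and d = 0.5 has effect 0.5/√1.8 = 0.373, which gives 46%. Adjustment at q = 0.6 has effect 0.5/√0.64 = 0.625, which gives 88%.

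**Sensitivity to equal SDs.** If the baseline SD is k times the follow-up SD, the change score has relative variance 1 + k² − 2rk. With k = 0.5 this is 1.15 at r = 0.1 and 0.95 at r = 0.3, so at d = 0.5 power is 65–73%. A compressed baseline removes most of the change-score penalty.

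**What the new covariate adds to a model that already holds the measured baseline.** With s the correlation between pre-fracture mobility and the acute baseline, R² = (r² + q² − 2rqs)/(1 − s²), and residual variance is multiplied by (1 − R²)/(1 − r²). Over the wider ranges r = 0.2–0.5, q = 0.3–0.7 and s = 0.2–0.4:
- Least gain (r = 0.5, q = 0.3, s = 0.4): R² = 0.262, ratio 0.738/0.75 = 0.98.
- Most gain (r = 0.5, q = 0.7, s = 0.2): R² = 0.625, ratio 0.375/0.75 = 0.50.

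The covariate may therefore cut residual variance by as little as 2% or as much as half.

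**How much of the change score is pre-fracture ability?** The share is (q − s)²/(2(1 − r)). Over the same wider ranges it runs from about 1% (r = 0.2, q = 0.3, s = 0.2: 0.01/1.6) to 25% (r = 0.5, q = 0.7, s = 0.2: 0.25/1.0). If the baseline had no spread at all the share would tend to q², which passes one half only for q above about 0.71.

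**The case against.** Several objections stand.

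- **Not only change.** A reader might infer that function is judged solely as change from baseline. The Statistics section also lists repeated-measures ANOVA and independent t tests, which can compare follow-up values directly. The change-score penalty therefore applies to one listed analysis, not to all. None of those listed names a covariate, however.
- **Not mostly prior ability.** It is tempting to say that change largely reflects how able patients were before the fall because everyone starts near the floor. The documents do not say that baseline values are near a floor, and patients are expected to stand on the platform from day 3. Correlations of 0.4–0.6 explain only 16–36% of follow-up variance (0.4² and 0.6²).
- **No bias.** Randomisation balances pre-fracture mobility in expectation. A chance imbalance is ordinary sampling error, already inside the standard error and the power figures, and should not be counted again.
- **Recovery can still be compared.** The objective concerns faster recovery, and serial measurements by arm can address it. Reading recovery as return to the pre-fracture level is a different endpoint, which the article does not adopt.
- **A condensed article.** The full protocol and any analysis plan are not shown. They may record pre-fracture mobility or name covariates, so silence here does not prove omission.

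These points limit the finding to efficiency and interpretation of secondary outcomes. They do not remove it: the analyses the article does state are unadjusted, and a better method is available at little cost.

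**Conclusion.** The point holds as a modest improvement to secondary outcomes. Every measured functional baseline is post-fracture, the article names no pre-fracture reference, and the stated analyses use no covariate. The between-arm comparisons are unbiased, and neither the primary outcome nor its sample size is affected.

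The size rests wholly on assumed correlations, effects and SDs. At d = 0.5 and 51 per arm, a change score could lose 15 to 25 percentage points of power against the follow-up value (71% against 46–56%), less if the baseline is compressed. Covariate adjustment could gain 7 to 17 points over the follow-up value (78–88% against 71%). The benefit may also be negligible: once the measured baseline is in the model, the cut in residual variance could be as little as 2%.

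**What to change.** 1. Unless the full protocol already does so, record pre-fracture walking ability (for example outdoors or indoors, and walking aid) after consent and before the envelope is opened, by patient or carer recall, checked against the CMS where it is noted.
2. Analyse the 6-, 12- and 26-week strength, balance, TUG and SF-36 values by ANCOVA, or an equivalent repeated-measures model, adjusting for the measured baseline and pre-fracture mobility. Use this in place of change-score ANOVA for the comparison between arms.
3. Report the proportion back at their pre-fracture walking level, by arm, as a descriptive supplementary result only. It should not become a new recovery endpoint.

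The cost is one short enrolment item and one extra covariate. Recall will carry some error, which weakens the covariate, but that error cannot differ systematically by arm because it is recorded before allocation. If the full protocol already collects the item, only the analysis text needs changing.
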